**Phase 1 – supervised group exercise 1 day/week + self-directed exercise at home 2 days/week for 12 weeks.**

Supervised group exercise.

Group exercise classes will be led by a qualified physiotherapist and delivered in the community (e.g., studios in fitness/leisure/wellbeing centres in Birmingham and Solihull).

The DT training programme requires participants to undertake concurrent cognitive and physical (balance and strength) exercise. Cognitive exercise will be delivered via a commercialised brain training app, PEAK. The content of the strength and balance exercises will align with the standard care. A study-specific account will be created for each participant so that no personal information will be shared with a third party, i.e., the app provider.

Prior to the face-to-face exercise class in week 1, all participants will receive online questionnaires to complete as their baseline data (see Outcomes below for details).

Week 1 exercise class will consist of a physical assessment of Timed Up and Go (TUG) with and without a cognitive task (see Outcomes below for details), app installation, the main DT exercise training, instruction of how to undertake the same exercises at home, and refreshment. The subsequent classes (week 2 to week 12) will consist of the DT exercise training, collecting self-reported adherence and app usage, refreshment, and individual technology support if needed.

With support from the physiotherapist, the PEAK app will be downloaded from the App Store or Google Play and installed on participants’ phones/devices. To start using the app, participants will take a cognitive assessment provided by the app and receive a brain score. The app will be set up to send notifications to the participants to remind them to exercise, supporting exercise engagement and adherence to the programme. Annual subscription fees for using the app will be purchased for all participants. This is sufficient to cover the length of the blended DT training programme (24 weeks).

In the supervised exercise class, all participants will undertake 10 minutes of strength and balance exercises alone (without a concurrent use of the app), as part of the warm-up to familiarise themselves with the movement of the exercises. This will be followed by 30 minutes of DT exercises where they will be doing the same strength and balance exercises while performing cognitive games with their device. The device will be placed on a height-adjustable music stand placed in front of the participants in an appropriate distance that allows them to use the app. The physiotherapist will provide individual support to the participants during the class to ensure everyone is able to engage with the DT exercise training. The class will be concluded with 5 minutes of cool down exercise.

At the end of the first group exercise class, the physiotherapist will provide each participant with a printout of the balance and strength exercises with pictures and instructions and instruct the participants to perform the same DT exercise training at home by themselves; a music stand will be provided to each participant. All participants will be provided an exercise calendar and shown how to document their exercise adherence outside of the exercise class. Refreshment will be provided at the end of each exercise class to promote attendance and contribute to participants’ social well-being^20,21^.

Participants will attend group exercise classes once a week for 12 weeks; their travel expenses for attending the classes will be paid. The class size will be 5-10 people.

Self-directed, home-based exercise.

Participants will be instructed to perform the same DT exercises at home on another two days per week. They can contact the research team for technical support. To record adherence, participants will be asked to tick the days that they have completed the DT exercise on their exercise calendar. The PEAK app will store data of when and which cognitive exercises are undertaken and completed. The exercise calendar will be returned to the physiotherapist or the research team at end of each month.

End of phase 1 – educational session.

Prior to the educational session, all participants will be sent an online EXIT survey (see below Outcomes section for details) and asked to complete the survey prior to the educational session.

All participants will attend an educational session for falls awareness scheduled in week 13 at the same time and same place as the exercise classes. Their travel expenses for attending the educational session will be paid. The app usage recorded from the two self-directed sessions in week 12 and the month 3 exercise calendar will be collected at the educational session. The content of the second phase of the intervention will also be explained in this session (see below for full description). Participants will be given an exercise booklet containing instructions of strength and balance exercises week-by-week and a 3-month exercise calendar. They will continue to have access to the PEAK app which will record their app usage and adherence from week 13 to 24.

Participants will be asked to consider ways that may help them stay motivated in doing the exercise in the next 12 weeks, such as creating WhatsApp groups or using Facebook Messenger, the most common messaging apps used by adults in the UK^22^, and supplemented by face-to-face “coffee shop” get-togethers to stay in touch with other participants in the same age and/or living in the same area. We will evaluate the impact of this informal peer support on engagement and sustainability of exercise as well as assess how peer support occurs in this age group, e.g., mostly in person or via social media in the planned focus groups (see below Qualitative interviews and focus groups section for details).

**Phase 2 – self-directed, home-based DT training programme 3 days/week for 12 weeks.**

Participants will undertake 30 minutes of self-directed DT exercises at home 3 times per week for 12 weeks. They will perform the DT exercise using the PEAK app and the strength and balance exercises in the exercise booklet. Usage and engagement of the app of the participants will continue to be recorded by the app. Participants will record their exercise adherence in the exercise calendar. Participants can contact the research team for technical assistance.

All participants will be contacted in week 24 to attend a post-assessment session in week 25. Their travel expenses for attending the post-assessment will be met.

End of Phase 2 (Week 25) – post assessment and app data extraction session.

Participants will be invited back to the same place of the exercise classes to undergo the TUG assessment. The research team will perform the TUG assessment and document the app usage data from week 13 to week 24 from participants’ phones/devices. The exercise calendars will also be collected from the participants. All participants will be sent the same online questionnaires as they completed at baseline and at the end of the phase 1 and asked to complete the questionnaires within 2 weeks from the post-assessment.

- **Qualitative interviews and focus groups**

Five face-to-face focus groups (FGs) with a total of 30 participants who have completed the programme (4-6 participants per group for 45-60 minutes) will be conducted. We will purposefully sample 30 participants, based on the demographic information, geographic location, exercise adherence, and results of the EXIT survey, to attend the focus groups.

Additionally, we will conduct five online FGs with a total of 30 healthcare professionals, including GPs, district nurses, paramedics, and physiotherapists who are part of the NHS falls prevention care pathways in Birmingham and Solihull, via MS Teams. Clinicians and physiotherapists involved in this study will be invited to take part.

The purpose of conducting the FGs is to allow for in-depth exploration of the results obtained from the feasibility study as well as to capture attributes of the acceptability and feasibility which are unable to be recorded by outcome measures stated in the feasibility study above. Questions will be developed based on the framework for qualitative research in feasibility studies for trials^23^ and input from the PPI group. Specifically, questions will cover 4 main categories:

- - Intervention content and delivery
  - Study design, conduct and processes
  - Outcomes (e.g., are they important to service users?)
  - Measures (e.g., are the process valid for the service users?)

Descriptive data from the adherence, usage of the app, and the EXIT survey will be used as prompts. The FG will be led by two members from the study team. The reason to have two people leading the FGs is to ensure both verbal and non-verbal interactions and group dynamics during the discussions can be documented^40^.

FGs will be voice recorded and later transcribed and analysed using a deductive thematic approach with Nvivo9 software; data for the study participants and the stakeholders will be analysed separately.

- 1. Assessments

**Primary outcomes:** Whether the study is appealing to participants (assessed by the recruitment rate) and if the intervention is acceptable (measured by adherence and usage of the app).

1. Recruitment via NHS falls prevention services and in community. The recruitment rate [(number recruited/number approached) x100%] will be assessed. Via the planned focus groups, we will investigate whether the recruitment route chosen in this study is appropriate for the main trial.

1. Usage of the app during the 24-weeks blended DT training programme:
   1. Numbers of days undertaking both cognitive and physical exercises and numbers of exercises completed, assessed via data extracted from the PEAK app cloud and recorded on the exercise calendars. App-recorded and self-reported adherence to the DT exercise will be compared to inform how to best record exercise adherence in the full trial.
   2. Types of cognitive exercises completed with the physical exercises, evaluated via the data extracted from the PEAK app, to provide information on content design of the DT training programme in the future.
2. Study retention rate: [(number completed study/ number recruited) x100%] will be assessed.
3. Usability, perceived effectiveness and satisfaction from a self-reported online EXIT survey based on the feasibility assessment framework (Technical, Economic, Legal, Operational, and Schedule)^24^. Data will be collected at the end of the phase 1 and 2. Exampled questions are as follows:
   - Overall, how beneficial did you find the training to be?
   - How easy was it to fit the training in to your daily routine?
   - Which of the following did you enjoy about the app?
   - Which of the following limited your use of the app?
   - How happy were you with the level of improvement of balance between the start and finish?
   - Have you noticed any other physical benefits or improvement after completing 6 months of the blended DT training?
   - Were you happy with the way your data being stored and collected by the PEAK?
   - Do you think the blended DT training programme with PEAK is a good way of achieving the above?
   - Did you receive the support you needed during the programme?
   - How likely will you continue with the training after the study completion?
   - If you were to continue with the training, how regularly do you think you would do it?
   - What could we have changed or improved?

The EXIT survey will be an online survey which will be uploaded through REDCap, which is secure encrypted data management software. We will use the REDCap managed by the Birmingham Centre for Observational and Prospective Studies (BiCOPS).

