- Adherence: Defined as the number of actual exercise days/number of exercise days offered (x100%) (60 days in total offered: 2 days/week x 12 weeks in phase 1 + 3 days/week x 12 weeks in phase 2) based on the exercise calendar.
- Usage of the app: Defined as the number of days used/number of days offered (x100%) and a self-reported online EXIT survey designed based on the feasibility assessment framework.
- Attrition: Defined as withdrawal from the study and/or no follow-up data available.

The secondary outcome measures will be: 1) Timed up and Go with and without a cognitive task, 2) everyday Cognition scales short version, 3) Falls Efficacy Scale-International, 4) Health questionnaire EQ-5D-5L, 5) Use of healthcare service via ModRUN, and 6) Self-reported numbers of falls.

1. Study design and methods of data collection and data analysis
   1. Study design

A single-arm, non-randomised feasibility study.

- 1. Recruitment

Recruitment will be carried out through the NHS falls prevention services, GP practices, and in community.

*NHS recruitment*

We will recruit from outpatient falls clinics at University Hospitals Birmingham and falls prevention services at the Birmingham Community Healthcare NHS Foundation Trust and Birmingham and Solihull Clinical Commissioning Group. These services receive patients living in different areas of Birmingham and Solihull, allowing recruitment of a diverse population. Additionally, e-searches on database of the NHS primary care in the West Midlands will be carried out by the primary care team of the CRN West Midlands. Text messages will be sent out to eligible participants.

For the site of Birmingham Community Healthcare NHS Foundation Trust and the GP practices in the West Midlands, a mail-out approach or SMS text messages will be used and carried out by an appropriate team in the Trust. Eligible participants will be identified from the database and sent a study flyer with the contact information of the research team for which they can reach out and enquire the study. Consent to enter the study will be sought at a community centre where the baseline assessment is being conducted.

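### Phase 2 exercise calendars, and app usage if read from devices, are gathered only at the week-25 visit with no route for non-attenders, so attenders-only figures may overstate adherence and usage

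*Protocol*

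**What the plan says.** Adherence and app usage are the two acceptability measures within the primary outcome, and both feed the stop-go decision (protocol, section 4.3). Adherence is taken from the exercise calendar over "60 days in total offered: 2 days/week x 12 weeks in phase 1 + 3 days/week x 12 weeks in phase 2".

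The means of collection differ by phase and by section:

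- **Phase 1 (section 5.3).** Self-reported adherence and app usage are collected at the weekly classes from week 2. For the calendar, "The exercise calendar will be returned to the physiotherapist or the research team at end of each month". The month 3 calendar and the week 12 app usage are picked up at the week-13 educational session.
- **Phase 2 (section 5.3).** In week 13 participants are given "a 3-month exercise calendar". They are contacted in week 24 and invited to a session in week 25, where the team will "document the app usage data from week 13 to week 24" from their phones or devices. At the same session, "The exercise calendars will also be collected from the participants".
- **Outcome definition (section 5.4).** Days and exercises completed are "assessed via data extracted from the PEAK app cloud and recorded on the exercise calendars".
- **Accounts (section 5.3).** "A study-specific account will be created for each participant".

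Section 5.5 plans to assess app usage in phase 1 and phase 2 separately, to understand any change between them. The repeated contacts in section 9 concern questionnaires. They are not extended to calendars or device readings.

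**The concern.** Capture drops from weekly and monthly contact to a single invited visit just when supervision ends. Attendance at that visit is plausibly related to the quantity being measured: someone who gave up the home exercise in week 15 has less reason to come back in week 25. The calendar, and the usage record if it is read from the device, would then be missing for the people whose behaviour matters most to the feasibility question.

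Three results are exposed:

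- the phase 2 adherence and usage estimates, which bear on the protocol's stated gap in knowledge about how well engagement is sustained (section 3);
- the comparison of phase 1 with phase 2 usage, which could mix a change in behaviour with a change in who is observed;
- the planned comparison of app-recorded with self-reported adherence (section 5.4), which would lose the same people from both sources if devices are used.

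An analysis plan can choose how to treat missing days, but it cannot recover a calendar that was never returned.

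**Working it through.** **The plan's own figure.** Section 7.2.1 gives an attrition rate of 20% in 50 participants with a 95% interval of +/-11%. Check: 1.96 x sqrt(0.20 x 0.80 / 50) = 0.111, so it reproduces. At 20%, 10 of 50 could lack phase 2 data, leaving 40.

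**Share of the adherence measure at risk.** Phase 1: 2 x 12 = 24 days. Phase 2: 3 x 12 = 36 days. 36/60 = 60%.

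**Inputs for the illustration.**
- m = share not attending week 25 = 20%, borrowed from the attrition benchmark.
- a = adherence of attenders = 80% (assumed).
- b = adherence of non-attenders = 20% (assumed; range 0% to 40%).

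The protocol gives no value for a or b in this programme.

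**Phase 2 alone.** True value = (1 - m)a + mb. The attenders-only estimate is a, so the overstatement is m(a - b).
- b = 20%: 0.8 x 80 + 0.2 x 20 = 68%, against 80%: 12 points.
- b = 40%: 64 + 8 = 72%: 8 points.
- b = 0%: 64 + 0 = 64%: 16 points.
- b = 80% (no difference): 0 points.
- m from 10% to 31% (20% plus the 11-point half-width), b = 20%: 0.10 x 60 = 6 points to 0.31 x 60 = 18.6 points.

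**All 60 days.** Assume the same a and b in both phases, all phase 1 days observed, and phase 2 days observed for attenders only. In person-equivalents, phase 1 contributes 40 x 0.8 + 10 x 0.2 = 34 and phase 2 contributes 40 x 0.8 = 32.
- Available days: (24 x 34 + 36 x 32) / (24 x 50 + 36 x 40) = 1968 / 2640 = 74.5%, against 68%: about 6.5 points.
- b = 40%: (24 x 36 + 1152) / 2640 = 76.4%, against 72%: 4.4 points.
- b = 0%: (24 x 32 + 1152) / 2640 = 72.7%, against 64%: 8.7 points.

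If non-attenders were dropped altogether, phase 1 included, the 60-day gap would return to 12 points.

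**Counting unrecorded days as not done.** The phase 2 estimate is (1 - m)a = 64%, so the error is -mb: 4 points too low if b = 20%, 8 too low if b = 40%, nil if b = 0%. Over 60 days it is 1968 / 3000 = 65.6%, against 68%: 2.4 points too low.

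**Bounds that assume nothing about non-attenders.** With attenders at 80%, phase 2 adherence in all 50 lies between 0.8 x 80 + 0 = 64% and 64 + 20 = 84%. That 20-point width comes from uncollected data.

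**The case against.** A reader might infer that the primary adherence and usage estimates are biased upward as the plan stands. The documents do not support that. An upward bias needs two things: an analysis confined to attenders, and lower adherence among those who stay away. The protocol states neither. Both measures are defined over days offered, and if days without a record were counted as zero the error would be nil or downward. That choice may properly sit in an analysis plan that is not shown.

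Nor is it right that app usage can only be had at the visit. Section 5.4 names the cloud, each participant has a study-specific account, and section 5.3 says the app goes on recording in weeks 13 to 24. For usage the defect is a conflict between two sections. For calendars the single visit stands, and because adherence is defined from the calendar, cloud data do not repair it.

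The monthly return and the 3-month calendar might also look contradictory. They belong to different phases, so this is an asymmetry between phases.

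Other mitigating points are fair. All participants are contacted in week 24 and travel is paid. The EXIT survey, part of the usage definition, is online and does not depend on attendance. Attrition and retention are reported, so the loss would be visible. The 20% is a stop-go benchmark for attrition and not a forecast of week-25 non-attendance, and the 12 points concern phase 2 alone.

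What remains is that no route is stated for a non-attender's phase 2 calendar, and that two sources are named for phase 2 usage. Seeing the attrition does not supply the missing adherence.

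**Conclusion.** The point holds as a gap in data collection with a conditional bias. Phase 2 calendars, carrying 60% of the adherence days, depend on one invited visit, and app usage does too if section 5.3 is followed over section 5.4. If only attenders' data are then analysed, adherence and usage may be overstated. On the assumed 80% and 20% with 20% non-attendance, the size is 12 points for phase 2 (8 to 16 as non-attenders range from 40% to 0%) and about 6.5 points over all 60 days (4.4 to 8.7). It is nil if non-attenders exercised as much as attenders. The size rests wholly on those assumed values; the missing collection route does not. The change is worth making because it is cheap and because analysis cannot restore records that were never collected.

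**What to change.** 1. Reconcile sections 5.3 and 5.4 on the source of phase 2 app usage. Make extraction through the cloud from the study-specific accounts the main route for every recruited participant, whether or not they attend week 25, with device reading at the visit as backup. Section 5.4 implies that the team can reach account data without the device; this should be confirmed before it is relied on.
2. Give phase 2 calendars a monthly return that does not depend on attendance: by post, by photograph, or by entry in REDCap.
3. In section 5.5, report adherence and usage for all recruited participants, with the available-data figure beside a lower bound that counts unrecorded days as not done. The lower bound should not be the sole estimate, because it errs downward whenever non-attenders did some exercise. State how many participants supply phase 2 data from each source.

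The cost is some wording in sections 5.3 to 5.5, a monthly reminder to participants, and possibly a less favourable adherence figure.

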## Roles and responsibilities of study management committees/groups and individuals

Patient & Public Involvement Group: [name] is a public co-investigator who will lead the patient and public involvement group and oversee the study to ensure outcomes meet patient benefits and interests. Participants in this study will be invited to a focus group to discuss their perspectives to the study. Discussion will be used for development of a follow-on study.

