Our observational study showed improved balance after a home-based DT training programme with a mobile app in older adults without a history of falls and the adherence rate over the 6-weeks training period was 90%^12^. A recent, underpowered RCT with older people in Australia reported a trend for improvement in walking speed after a homebased DT programme via tablets^11^. These findings support the notion that technology-based exercise (not limited to DT exercise) may be a sustainable means of promoting physical activity and preventing falls in older people^17-19^. However, the evidence is not definitive in how sustained the engagement and the effectiveness of the DT training programme with technology can be. This study contributes to the need to identify a delivery method for home-based exercise using mobile apps that is acceptable to older people and has the potential to be adopted by the NHS.

1. Research question/aims
   1. Research aim

- This study aims to examine how feasible it is to deliver a blended supervised and self-directed technology-based DT training programme for older adults who have high risks of falling and wish to improve balance and mobility.
  1. Research questions
- Is a 24-weeks blended supervised and self-directed technology-based DT training programme (using a mobile app) acceptable to older people at risk of falling? Secondary research questions
- Is a 24-weeks blended supervised and self-directed technology-based DT training programme feasible and deliverable, with potential to be adopted by falls prevention services in the NHS?
  1. Outcomes

The primary outcome will be the feasibility of a subsequent phase III trial according to pre-specified progression criteria. We are primarily interested in whether the study is appealing to participants (assessed by the recruitment rate) and if the intervention is acceptable (measured by adherence and usage of the app).

The decision of whether to continue to the phase III trial will be decided by pre-defined stop-go criteria, based on the following definitions and criteria:

- Recruitment via NHS fall prevention service and in community: Defined as the number recruited/number approached (x100%). Via the planned focus groups, we will investigate whether the recruitment route chosen in this study is appropriate for the main trial.

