For the other sites, adults meeting the eligibility criteria will be approached by a clinician in the falls clinic and provided with a study information leaflet which contains study information and contact details of the research team. The clinician may inform the research team that the participant has agreed to take part in the study and has agreed to be approached. The research team will then approach the participant to answer questions they might have and complete informed consent procedures. Alternatively, the participant can ring the research team to express willingness to take part and/or ask questions.

Furthermore, we will recruit 30 healthcare professionals working in the NHS falls prevention services in England and Wales for focus groups. We will advertise the study participation opportunity via professional bodies and social media.

Community recruitment

We will put up the study flyer in retirement homes, book clubs, etc in the West Midlands. Potential participants will be able to self-refer to members of the research team.

- 1. Planned interventions

A summary of the blended DT intervention is in Table 1:

Table 1. Summary of the blended DT exercise training programme.

|  | Supervised group exercise | Self-directed, home-based exercise |
| --- | --- | --- |
| Phase 1 – week 1-12 | **Duration:** 45 minutes  **Location:** local leisure/wellbeing centres  **Frequency:** one class/week  **Content:** 10 minutes warm-up, 30 minutes of DT training, 5 minutes cool down, followed by refreshment.  **DT training:**   - Cognitive exercises delivered via the PEAK app. - Strength and balance exercises delivered by a physiotherapist | **Duration:** 45 minutes  **Location:** at home  **Frequency:** twice/week  **Content:** 10 minutes warm-up, 30 minutes of DT training, 5 minutes cool down.  **DT training:**   - Cognitive exercises delivered via the PEAK app. - Strength and balance exercises in an exercise booklet |
| Phase 2 – week 13-24 | No supervised group exercise | **Duration:** 45 minutes  **Location:** at home  **Frequency:** three/week  **Content:** 10 minutes warm-up, 30 minutes of DT training, 5 minutes cool down.  **DT training:**   - Cognitive exercises delivered via the PEAK app. - Strength and balance exercises in an exercise booklet |

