6. Are self-toileting,
7. Own or have access to a smartphone/iPad/iPod touch/tablet, and
8. Have fallen more than once in the last 12 months.
   - 1. Exclusion criteria

Patients will be excluded if they:

1. have an unstable or acute medical condition that precluded exercise participation,
2. suffer from a progressive neurological condition (such as Parkinson’s disease or multiple sclerosis),
3. are not recommended to undertake any forms of exercise by their GPs or secondary healthcare team; for example, having uncontrolled blood pressure, postural hypotension, acute/unstable cardiac issues, and dizziness brought on by exercise or changing posture. or
4. are currently participating in a different research study for managing their fall risks.

Additionally, the inclusion criteria for recruiting stakeholders to the qualitative focus group study are:

- - Aged 18 years and above,
  - A healthcare professional in the NHS falls prevention care pathways in the Birmingham and Solihull.

Healthcare professionals with less than 6 months experience in the falls prevention care pathways will not be recruited.

- 1. Recruitment target
     1. Size of recruitment target

A sample size of 50 was chosen based on published literature where a sample size of between 50 and 100 participants (total; i.e. 25 to 50 per group) is recommended for pilot studies42-44. If we identify 100 eligible participants, we will be able to estimate a participation rate of 50% (green stop-go; see below) within a 95% confidence interval of +/-9.8%. With a sample size of 50 participants, we will be able to estimate an attrition rate of 20% (green stop-go; see below) to within a 95% confidence interval of +/-11%.

- - 1. Recruitment technique

Clinicians in the falls team will screen and identify eligible participants for the study. The potential participants will be provided a study flyer with contact information of the research team to enquire study information if they wish. Clinicians or research nurses in the NHS sites may mail out study flyers or send out text messages to eligible participants who will be able to self-identified themselves and contact the research team.

- 1. Recruitment
     1. Participant identification

Identification of suitable participants will be carried out through falls clinics at the University Hospitals Birmingham and falls prevention services at the Birmingham Community Healthcare NHS Foundation Trust and Birmingham and Solihull Clinical Commissioning Group.

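### The participant focus groups, the only in-depth qualitative source from participants, are limited to people who completed the programme, so they are likely to lean favourable on acceptability

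*Protocol*

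**What the plan says.** Section 5.3 (Qualitative interviews and focus groups) sets up "Five face-to-face focus groups (FGs) with a total of 30 participants who have completed the programme". Selection within that pool is purposive: "We will purposefully sample 30 participants, based on the demographic information, geographic location, exercise adherence, and results of the EXIT survey". The same section gives the groups two tasks: to explore the feasibility results in depth, and to "capture attributes of the acceptability and feasibility which are unable to be recorded by outcome measures stated in the feasibility study above". Its heading mentions interviews, but none is described.

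The section on roles and responsibilities states no completion condition: "Participants in this study will be invited to a focus group to discuss their perspectives to the study".

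Section 4.3 asks whether the study appeals to participants and "if the intervention is acceptable (measured by adherence and usage of the app"). It also defines attrition, as withdrawing, lacking follow-up data, or both. Section 5.4 adds a retention rate and an EXIT survey at two fixed times, the ends of phases 1 and 2.

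For the professional groups, section 5.2 states that "we will recruit 30 healthcare professionals working in the NHS falls prevention services in England and Wales for focus groups". The eligibility criterion in section 7.1 is "A healthcare professional in the NHS falls prevention care pathways in the Birmingham and Solihull", and section 5.3 likewise describes professionals from the Birmingham and Solihull pathways.

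**The concern.** The first research question is whether a 24-week programme is acceptable to older people at risk of falling. The people best placed to say what made it unacceptable include those who stopped, and section 5.3 leaves them out of the one component designed to find out why. Sampling on adherence and EXIT results adds variety among people who stayed. It cannot bring in anyone who left.

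What is at stake is the redesign before a phase III trial. If technology, travel, exercise burden or health led people to leave, the focus groups would hear of it only from people who got past those obstacles.

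The professional groups have a separate problem. A respondent from outside Birmingham and Solihull fits section 5.2 but fails the criterion in section 7.1. The second research question concerns adoption by NHS falls prevention services, so the frame determines how far that conclusion reaches.

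**Working it through.** **1. Where a leaver can appear in the evidence on acceptability**

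| Source | Can a leaver contribute? | Does it give reasons? |
| --- | --- | --- |
| Attrition (4.3), retention (5.4) | Yes, counted directly | No |
| Adherence, app usage (4.3, 5.4) | Yes in principle, since the denominator is days offered | No |
| EXIT survey, end of phase 1 (5.3, 5.4) | Yes, if the person left in phase 2 | Partly: it asks about limits on app use, fit with daily routine and support |
| EXIT survey, end of phase 2 (5.4) | No contact at the time of withdrawal is described; one example item presupposes six completed months | Unlikely |
| Focus groups (5.3) | No | Yes, for completers |

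The adherence and usage row has a limit. Under section 5.3, phase 2 calendars and app data read from devices are collected at the week 25 visit, so leavers' records may be incomplete. The monthly calendar return in section 5.3 and the app cloud data in section 5.4 reduce this.

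**2. The plan's own precision figures (section 7.2.1)**

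Half-width = 1.96 × √(p(1 − p)/n).

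- Attrition, p = 0.20, n = 50: 1.96 × √(0.16/50) = 0.111. The stated ±11% is reproduced.
- Participation, p = 0.50, n = 100: 1.96 × √(0.25/100) = 0.098. The stated ±9.8% is reproduced.

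**3. Illustration of how many people are excluded**

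Assumptions: 50 people start, and the proportion not completing equals the attrition proportion. The protocol states neither as a forecast.

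| Proportion not completing | Leavers | Completers | 30 places as share of completers |
| --- | --- | --- | --- |
| 8.9% (20% − 11.1%) | 4.5 | 45.5 | 66% |
| 20% | 10 | 40 | 75% |
| 31.1% (20% + 11.1%) | 15.5 | 34.5 | 87% |
| 40% | 20 | 30 | 100% |

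At 20%, about 10 people have no chance of selection, with a range of about 4 to 16. If places were open in proportion, leavers would hold about 30 × 0.20 = 6; under section 5.3 they hold none.

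**4. Alternative reading of the 50**

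Section 10.8 ends the study when 50 participants have completed. If 50 means completers, 20% not completing implies 50/0.80 = 62.5, or about 63 starters, and about 13 people excluded.

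**5. The professional frame**

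Section 5.2 gives England and Wales, while sections 5.3 and 7.1 give Birmingham and Solihull. As written, these cannot all be followed.

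**The case against.** A reader might infer that all of the acceptability evidence excludes people who left. The documents do not support that. Acceptability is defined through adherence and app usage, leavers are counted in attrition and retention, and the end-of-phase-1 EXIT survey goes to all participants. The restriction applies to the in-depth qualitative component.

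A reader might also take 10 non-completers as the expected number. The 20% is the green stop-go value in a precision statement. Attrition as defined also differs from not completing the programme: someone may finish the exercises and miss week 25, or stop exercising and still attend. The count is therefore only an illustration.

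Nor does the shortage of room for purposive selection come mainly from the completer rule. It comes from taking 30 of about 50 people. With 6 places for 10 leavers and 24 for 40 completers, 60% of each group would still be needed.

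A further tempting inference concerns the recruitment route, because the plan says "Via the planned focus groups, we will investigate whether the recruitment route chosen in this study is appropriate for the main trial". Programme leavers were successfully recruited, so excluding them is not what limits that question. People who declined would be the informative group, and they are a different matter.

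Other points on this side stand in part. Completion carries no adherence threshold, so poorly adherent or dissatisfied people who stayed can be chosen; this softens the favourable lean but does not remove it. The flow chart and consent material are not available here, so arrangements for withdrawal described there cannot be ruled out. On the professional side, local NHS staff can speak to adoption in their own services, so the local frame is not worthless.

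**Conclusion.** The point holds for the focus groups. As section 5.3 is written, the only in-depth account of acceptability from participants comes from completers, and nothing visible in the protocol replaces the missing view. The other measures record that people left; only the phase 1 EXIT survey offers partial reasons, and only from those who left after it. The focus-group findings are therefore likely, though not certain, to lean favourable.

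The size cannot be fixed from the documents. About 10 of 50 people excluded (about 4 to 16) is an illustration that rests on 50 starters and on equating non-completion with the 20% attrition value. The argument does not depend on that number.

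Two inconsistencies need no assumption: the roles section and section 5.3 differ on who is invited, and section 5.2 conflicts with sections 5.3 and 7.1 on which professionals are eligible.

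**What to change.** - In section 5.3, open the participant groups to people who started the programme. Keep the total of 30, and hold some places for people who withdrew or stopped exercising and are willing to take part, by phone or online if they prefer.
- Offer the online EXIT survey at withdrawal. Make it optional, remove items that presuppose completion, and respect the right in section 7.3.2 to give no reasons.
- Align the roles section with the revised section 5.3.
- Choose one frame for the professional groups, use it in sections 5.2, 5.3 and 7.1, and limit the conclusion on adoption to that frame.

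The cost is modest: wording changes, coverage in the consent material, a short withdrawal version of an existing survey, and a small second mode of data collection beside the face-to-face groups. No additional focus-group places are needed. Some leavers will decline, so the gap will narrow but not close.
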